## Abstract

**Background:**

Up to 75% of inpatients with mental disorders smoke, and their life expectancy is decreased by up to 25 years compared to the general population. Hospitalized patients without monitoring after discharge quickly return to prehospitalization levels of tobacco use. The aim of the 061 QuitMental study is to assess the effectiveness of a multicomponent and motivational telephone-based intervention to stop smoking through a quitline addressed to smokers discharged from mental health hospital wards.

**Methods:**

A pragmatic randomized controlled trial, single blinded, will include 2:1 allocation to the intervention group (IG) and the control group (CG). The IG will receive telephone assistance to quit smoking (including psychological and psychoeducational support, and pharmacological treatment advice if required) proactively for 12 months, and the CG will receive only brief advice after discharge. The sample size, calculated with an expected difference of 15 points on smoking abstinence between groups (IG, 20% and CG, 5%), α = 0.05, β = 0.10, and 20% loss, will be 334 participants (IG) and 176 participants (CG). Participants are adult smokers discharged from psychiatric units of five acute hospitals.

Measurements include dependent variables (self-reported 7-day point prevalence smoking abstinence (carbon monoxide verified), duration of abstinence, number of quit attempts, motivation, and self-efficacy to quit) and independent variables (age, sex, and psychiatric diagnoses). In data analysis, IG and CG data will be compared at 48 h and 1, 6, and 12 months post discharge. Multivariate logistic regression (odds ratio; 95% confidence interval) of dependent variables adjusted for potential confounding variables will be performed. The number needed to treat to achieve one abstinence outcome will be calculated. We will compare the abstinence rate of enrolled patients between groups.

**Discussion:**

This trial evaluates an innovative format of a quitline for smokers with severe mental disorders regardless of their motivation to quit. If effective, the pragmatic nature of the study will permit transfer to routine clinical practice in the National Health System.

**Trial registration:**

ClinicalTrials.gov, NCT03230955. Registered on 24 July 2017.

**Electronic supplementary material:**

The online version of this article (10.1186/s13063-018-3106-5) contains supplementary material, which is available to authorized users.

## Key points

This study is the first designed specifically for mental health patients with a long-term follow-up of 1 year, as other studies have performed follow-up periods of 6–7 months maximum.This trial evaluates an innovative quitline for smokers with severe mental disorders regardless of their motivation to quit.If effective, the pragmatic nature of the study will permit transfer to routine clinical practice in the National Health System.

## Background

Smoking prevalence has declined over the last decade in developed countries. However, in some vulnerable populations, such as people suffering from mental disorders, the prevalence has not followed this trend [1–3]. People with mental disorders are more likely to smoke, and the greater number of lifetime psychiatric diagnoses, the greater the probability of smoking [4]. In Catalonia, 74.4% of patients hospitalized for mental disorders smoke [5], which is three times higher than the smoking rate (26.9%) in the general population [6]. In addition, these patients start to smoke at an early age, experience higher levels of nicotine dependence, and have more difficulty quitting [7, 8].

The reasons for higher consumption of tobacco among people with mental disorders are not clear. Several explanations have been suggested, including genetic factors or/and a low socioeconomic level [9]. Another explanation sometimes invoked is the self-medication hypothesis, which suggests that patients with mental disorders, and particularly those with schizophrenic diagnoses, smoke to ameliorate their symptoms. However, this hypothesis is increasingly rejected [10, 11].

Tobacco is the cause of death for 48–53% of people with mental illness [12, 13] primarily for cardiovascular and respiratory diseases, cancer, and diabetes [14]. For people with severe mental illness, life expectancy is reduced up to 10–17 years, mainly for illnesses caused or worsened by smoking [15–17]. The persistent high prevalence of tobacco use within this population highlights how public health and healthcare services have neglected the needs of this disadvantaged population [18]. Historically, tobacco consumption has been considered a “minor problem” among patients with mental disorders; it was believed that these patients were not interested in quitting [19] and even that smoking helped patients control their disorder [20]. Some of these beliefs may be reflected in smoking cessation research. While there have been approximately 9000 smoking cessation trials among general population smokers, there have been only 20 such trials among patients with mental disorders [21]. The few studies that have been done, however, indicate that patients with mental disorders can achieve significant rates of abstinence [20].

Over the last decade, some jurisdictions have implemented cost-effective measures, as proposed by the World Health Organization (WHO), to curb smoking among persons with mental disorders [20]. These measures are mainly policies for smoke-free areas, treatment to quit smoking, and community measures of sustained support to quit [22].

Hospitalization in smoke-free psychiatric centers increases the quality of life in both patients and professionals, and decreases the exposure to second-hand smoke [23]. In addition, such policies increase quit attempts by patients and their expectations of staying abstinent [24, 25]. Only total smoke-free areas completely protect patients from second-hand smoke [26]. In Spain, the tobacco control Law 42/2010 bans smoking in both indoors and outdoors areas of acute hospitals including psychiatric units. This legal framework, which implies abstinence of patients during hospitalization, creates a unique opportunity to promote smoking cessation among patients with mental disorders.

Concerning treatment to quit smoking, the use of self-help materials, telephone advice, and psychological and pharmacological treatments have been shown to be effective [27, 28]. Although interventions to promote smoking cessation among patients with mental disorders aim to achieve abstinence, it is often necessary to first promote motivation to quit [27]. Thus, these patients would be able to make serious attempts to quit smoking when hospitals have trained professionals to respond to their needs and offer them pharmacological and psychological aids [29]. Interventions that combine pharmacological treatment and psychological therapy—primarily cognitive-behavioral psychological treatment—increase the likelihood of tobacco cessation in patients with mental disorders [30–32]. However, without patient monitoring after discharge, smoking is restored to previous levels in 2 weeks [33, 34]. Only a few clinical trials [21, 35, 36] have demonstrated the efficacy of multicomponent interventions (which included motivational, psychosocial, and pharmacological components) addressed to patients with mental disorders after discharge. In these studies, the intervention group showed higher abstinence rates, more quit attempts, and fewer cigarettes per day as compared to controls [21, 35, 36]. In addition, as shown in the general population, it is likely that patients with a mental disorder who quit smoking also reduce their levels of anxiety, increase their quality of life, and obtain better results in abstinence from other drugs [37].

In relation to community measures, “quitlines” (i.e., telephone counseling) stand out as an effective support in the general population [38]. However, this resource has so far been little used among populations with mental disorders [39]. The few studies conducted with mentally ill patients showed that a quitline intervention combined with nicotine replacement therapy (NRT) slightly but significantly increased 7-day point prevalence abstinence at 6 months follow-up, reduced the number of cigarettes consumed per day, and increased readiness to quit smoking [36, 39].

In Catalonia, the health information and care telephone line “061 CatSalut Respon” provides a free support program to quit smoking, which acts as a quitline. A nursing team, experts in telephone assistance and smoking cessation, provide an individualized intervention to quit smoking through intensive care for 1 year. However, this service has not so far been used for patients with mental disorders. Quitlines may have some advantages over other cessation services, as they can increase access, are less costly than face-to-face visits [38], and offer a solution to the lack of systematic interventions in patients with mental disorders especially after discharge [34, 40]. However, contact with the quitline is usually initiated by the smoker, and is not usually initiated proactively by the treatment provider. Therefore, we propose a pragmatic randomized controlled trial that uses the existing resources of 061 CatSalut Respon to engage patients with mental disorders identified during hospitalization in acute psychiatric hospital units.

The aim of this study is to assess the effectiveness of a telephone-based (quitline) intervention for smoking cessation addressed to smokers with severe mental disorders after discharge from adult inpatient acute units (the 061 QuitMental study). The intervention group (IG) will receive a telephone intervention to quit smoking (including psychological and psychoeducational support and pharmacological treatment advice, if required) proactively for 12 months, and the control group (CG) will receive only brief counseling after discharge.

The specific objectives of the 061 QuitMental study are as follows:to assess the effectiveness of the intervention in relation to the characteristics of the smokers (mental disorder, comorbidity, age, sex, and educational level and occupation);to compare the levels of motivation to quit smoking, self-efficacy, attempts to quit smoking, and the likelihood of smoking abstinence in the intervention group and the control group;to describe the use and satisfaction with the quitline in the intervention group and the control group; andto assess the feasibility of this intervention to systematically offer it at a community level.

These objectives will be analyzed by comparing the results obtained from the IG and the CG at several time points post discharge: 48 h and 1, 6, and 12 months (Fig. 1).

**Fig. 1 Fig1:**
[figure not shown]
Study variables and collection time points. GHQ-12 12-item version of the General Health Questionnaire

The hypotheses of this study are the following:IG participants, as compared to CG participants, will demonstrate higher rates of biochemically verified 7-day point prevalence smoking abstinence, at all evaluation time points (48 h and 1, 6, and 12 months post discharge).IG participants, as compared to CG participants, will experience longer periods of sustained abstinence as demonstrated by sequential biochemically verified 7-day point prevalence smoking abstinence, at all evaluation time points.IG participants who continue to smoke, as compared to CG participants, will show greater reduction in the number of cigarettes smoked per day, at all evaluation time points.IG participants who continue to smoke, as compared to CG participants, will show an increase in the progression of their readiness to quit smoking, based on stages of change, at all evaluation time points.IG participants, as compared to CG participants, will have a higher level of self-efficacy to quit at all evaluation time points.

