### Variables

#### Outcome measures

##### Primary outcome measure

Self-reported 7-day point prevalence smoking abstinence, biochemically verified with expired carbon monoxide (CO) measures, is the primary outcome. Seven days of abstinence has been chosen as a consumption measure [41]. This variable will be recorded in every call of the intervention (48 h, 1 week, 15 days, and 1, 3, 6, and 12 months post discharge). Abstinent subjects at 1, 6, and 12 months in either of both groups (IG or CG) will be invited to attend a consultation at their hospital to verify their abstinence through the detection of exhaled carbon monoxide. The abstinence rate between the IG and the CG will be compared at 1, 6, and 12 months. In each call, nicotine withdrawal symptoms will be assessed according to the scale proposed by Hughes and Hatsukami [42].

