##### Secondary outcome measure

We will also record other smoking variables such as continuous abstinence. Moreover, for nonabstinent patients we will ask about their tobacco use (quantity), type of tobacco consumed (cigarette/cigar/other), number of quit attempts, and other variables included in the “smoking” section in Fig. 1. Moreover, using an ad-hoc Likert scale from 0 to 10 we will evaluate the level of self-efficacy to quit or reduce consumption, the intention to quit, and the intention to reduce consumption. The individual’s willingness to quit will be also evaluated according to the Prochaska and Di Clemente Stages of Change model, which measures four stages of readiness to quit smoking (precontemplation, contemplation, action, and maintenance) [43].

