### Procedure

The research team designed a telephone-based intervention with a proactive approach to help patients quit smoking after discharge from hospitals. The intervention will take into account the recommendations made by a group of experts in the design of telephone-based interventions (quitlines) aimed at patients with mental illnesses [39]. The intervention will also be based on the protocol of the general quitline of 061 CatSalut Respon and a clinical intervention guide for smoking cessation in patients with mental disorders [28]. Depending on the case, the intervention will be directed to: increase motivation to quit; achieve abstinence; prevent relapses if achieving abstinence; reduce consumption and increase motivation to quit smoking when the patient is still not ready or motivated to quit; and/or recommend pharmacological treatment.

The intervention will be conducted by 061 CatSalut Respon nurses within the first 48 h, 1 week, 15 days, and 1, 3, 6, 9, and 12 months after discharge. IG subjects will be contacted by the trained nurses and will provide an intervention strategy adapted to each patient situation in each call (whether they smoke, take pharmacological treatment to quit, are ready for a quitting day calls, “D day”, etc.) according to an algorithm procedure (Fig. 1). The first telephone call at 48 h will serve as a starting point for the quitline intervention outside the hospital and to take baseline data post discharge.

CG subjects will be contacted after the first 48 h following discharge by nonclinical telephone assistants who will provide brief advice (only in the first call) and collect data for comparison, at this time (48 h), 1, 6, and 12 months post discharge. The investigators trained the nonclinical telephone assistants in order to conduct the interviews in a neutral tone following the wording of each of the questions and not giving health recommendations, as they are not qualified to do so. For patients who express their desire to quit, telephone assistants suggest they talk with their outpatient clinic doctor, nurse, or psychologist to receive aid*.*

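### Hypothesis 2 takes three verified 7-day snapshots as proof of longer sustained abstinence, but they show neither its continuity nor its length

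*Protocol article*

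**What the plan says.** The hypotheses stand at the end of the Background of the protocol article, after Fig. 1. The second predicts that the intervention group will have "longer periods of sustained abstinence as demonstrated by sequential biochemically verified 7-day point prevalence smoking abstinence", and it applies this to every evaluation time point. The first hypothesis spells those time points out: "at all evaluation time points (48 h and 1, 6, and 12 months post discharge".

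The section on the primary outcome measure fixes the window ("Seven days of abstinence has been chosen as a consumption measure") and the verification schedule: "Abstinent subjects at 1, 6, and 12 months in either of both groups (IG or CG) will be invited to attend a consultation", where the CO test is done. No CO test is offered at 48 h. The Procedure section has the control-group assistants "collect data for comparison, at this time (48 h), 1, 6, and 12 months post discharge". The intervention group has eight calls: 48 h, 1 week, 15 days, and 1, 3, 6, 9 and 12 months.

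Two other places bear on the point. The section on secondary outcomes states: "We will also record other smoking variables such as continuous abstinence". The Abstract lists duration of abstinence as a dependent variable, separately from the 7-day measure. Neither place links these variables to hypothesis 2.

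**The concern.** Hypothesis 2 names both a conclusion (longer sustained periods) and the evidence for it (a sequence of verified 7-day point prevalences). This is a stated choice of measure, not a detail left for a later document.

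Point prevalence answers whether someone was abstinent in the week before an assessment. Repeating it months apart answers that question again; it says nothing about the months between. If the hypothesis is tested as worded, a group difference in the number of abstinent assessments could be published as a difference in how long participants stayed abstinent. The article's own Background shows why the distinction matters here: it reports that patients left unmonitored after discharge are back at their earlier consumption within 2 weeks.

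**Working it through.** The plan gives no figure for this point, so there is none to reproduce. The check is calendar arithmetic on the article's own schedule.

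**Inputs.** Verified assessments at 1, 6 and 12 months and a 7-day window (section on the primary outcome measure). One month is taken as 365.25 / 12 = 30.44 days, counted from discharge.

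**Windows.** Each runs from (month × 30.44 − 7) to (month × 30.44):
- 1 month: days 23.4 to 30.4
- 6 months: days 175.6 to 182.6
- 12 months: days 358.2 to 365.2

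**Coverage.** 3 × 7 = 21 days; 21 / 365.25 = 5.7% of follow-up.

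**Unobserved gaps.**
- 1 to 6 months: 175.6 − 30.4 = 145.2 days (4.8 months)
- 6 to 12 months: 358.2 − 182.6 = 175.6 days (5.8 months)

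For scale, the 2-week return to smoking cited in the Background fits about 145 / 14 = 10 times into the first gap and 176 / 14 = 12 times into the second. That figure describes unmonitored patients, so it is a yardstick and not a forecast for either arm.

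**What each pattern allows.** The longest unbroken abstinent period after discharge that is compatible with the verified results, taking a negative entry to mean smoking at that assessment:

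| 1 / 6 / 12 months | Count | Could be as short as | Could be as long as |
|---|---|---|---|
| + / + / + | 3 | 7 days | about 365 days |
| + / + / − | 2 | 7 days | about 364 days |
| + / − / − | 1 | 7 days | about 182 days |

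The ranges overlap almost completely, so the count need not even rank participants by duration. Someone who quits at month 7 and stays abstinent to month 12 has about 5 × 30.44 = 152 days and a count of 1. Someone who is abstinent only in the week before each assessment has 7 days at a time and a count of 3.

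**Extra intervention-group calls.** From 1 week on there are seven calls, hence at most 7 × 7 = 49 days of self-reported windows; 49 / 365.25 = 13%. The calls at 1 week, 15 days, 3 months and 9 months have no stated CO check and no control-group counterpart, so they cannot supply a verified comparison.

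**The 48 h point.** Hypothesis 2 requires biochemical verification at all evaluation time points, but none is offered at 48 h. A 7-day window ending then also reaches back about 7 − 2 = 5 days before discharge. For participants already admitted by then, those days fall in units where the Background says smoking is banned.

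**The case against.** The strongest reply is that the trial already plans what is needed. Continuous abstinence is a recorded secondary variable, duration of abstinence is a listed dependent variable, and the items collected at each call are set out in Fig. 1, which is not shown. On that view hypothesis 2 is only loosely worded. Much of this stands. A reader might infer that the trial has no measure of continuity, or that new call items are certainly needed; the documents support neither. What the reply does not remove is that hypothesis 2 names the sequence of point prevalences as its demonstration and does not use those variables.

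A second reply is that both arms share the same three verified points, so the coarseness is common to both and need not bias the comparison. This also stands as far as it goes: nothing here shows that a group difference would be created or reversed. A comparison of counts remains valid as a comparison of counts. It does not become a comparison of sustained periods.

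A reader might go further and infer that the intervention pushes short quit attempts at every call and so inflates apparent sustained abstinence in its own arm. The article does not say that. The Procedure section makes the aim depend on the case, including relapse prevention and reduction of consumption, and the section on the telephone intervention says the objectives adapt to smoking status at each call.

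Nor can an error in months be assigned to each participant. That would need a rule for turning the sequence into a duration, and the article states none.

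**Conclusion.** The point holds for hypothesis 2 as worded. Three verified 7-day windows cover 5.7% of the year, leave gaps of about 145 and 176 days, and are compatible with an unbroken abstinent period of anything from about 7 to 365 days in a participant verified every time. They support a statement about repeated point-prevalence abstinence at 1, 6 and 12 months, and no statement about continuity or length. At 48 h the verified measure does not exist.

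This rests on the stated schedule and on calendar months of 30.44 days; modest shifts in visit timing do not change it. It concerns a secondary hypothesis. The primary comparison of 7-day abstinence is unaffected, and no direction or size of bias between the groups is claimed. The change is worth making because it decides what the trial may say about lasting abstinence.

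**What to change.** Reword hypothesis 2 so that it rests on the continuous-abstinence and duration variables already listed. Count sustained abstinence at 6 and at 12 months only when the participant reports no smoking since the previous evaluation call and is CO-negative at the end of that interval. Collect this in the same way in both arms, at the calls that both arms share. Add the interval question to those calls only if Fig. 1 or the full protocol shows that it is not already asked.

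Report the sequential 7-day results at 1, 6 and 12 months under the name *repeated point-prevalence abstinence*, and do not claim verified abstinence at 48 h. If interval data cannot be obtained, make the relabelling alone and withdraw the claim about longer periods.

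The cost is a reworded hypothesis, a stated definition and possibly one short question in existing calls. The downside is that sustained-abstinence rates will be lower than the snapshot sequence suggests, and abstinence within each interval will rest on recall.

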## Methods

This project arises from the collaboration between the Catalan Institute of Oncology, the Public Health Agency of Catalonia, and the 061 CatSalut Respon program, which is a public telephone service from the National Health System about health topics addressed to all citizens.

